The session 6 exposure aims to help the participant evaluate the utility of safety behaviors in social situations. Participants complete a social activity twice, once using safety behaviors and once without, to challenge their fears about dropping safety behaviors and explore the impact of using them in social situations [originally from Clark et al.’s cognitive therapy, (71)]. Therapists are instructed to choose a social activity that takes no longer than 5 min, to make the experiment practical to complete in a timely manner. Examples may include the participant interacting with the therapist (role play) or person from around the clinic.

The session 7 exposure aims to correct participant’s negative self-perception. The participant delivers a recorded speech and then reviews how they appeared compared to what they expected [similar to the procedure in Harvey et al. (72)]. Therapists may tailor the experiment to participants by adjusting the difficulty (for example, choosing a less familiar topic, arranging more audience members, or affording less preparation time).

The session 8 exposure aims to give participants practice focusing their attention on the task during social situations, rather than on the self or what the other person is thinking. Therapists are advised to choose a social interaction activity such as a role-play conversation with a therapist or colleague or making small talk with someone near the clinic. In-session exposures for sessions 5, 6, 7, and 8 can be conducted over video teleconference through role plays with the therapist or inviting confederates to the video call as needed.

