Session 9 is devoted entirely to guided exposure where the participant attempts various exposures outside of the clinic with the support of their therapist. These exposures focus on the participant deliberately doing socially “odd” or notable behaviors to see what happens compared to their fears. Participants are supported to choose two exposures to complete with the therapist and two to complete individually during the session. A list of choices is provided but bespoke exposures can be developed in collaboration with the participant. An example of a paired exposure is the therapist and participant looking upwards and pointing for 5 min. An example of an individual exposure is to ask a shop assistant where an item is while standing in front of it. This session can be facilitated by the therapist over the phone or video teleconference as needed, where the participant completes the above exposures *in situ* with the therapist “in their pocket.”

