### Analysis

The relationship between exposure processes and outcome variables over time will be explored using univariate multilevel modeling (MLM). This modeling framework has a range of strengths for our purposes. It can account for data dependencies typical in longitudinal designs, can handle assessment schedules that are unevenly spaced, and can handle unbalanced data (88). Prediction error is the exposure process of interest. We operationalize prediction error as the discrepancy between threat prediction (P) and threat outcome (O) scores for an exposure.

Prediction error effects can only be explored if enough cases of prediction error exist in the data. We will explore how many cases of prediction error and what type are present in the data before modeling. For descriptive purposes, we will categorize a prediction error as an exposure where the standardized P and O scores differ by more than 0.5 standard deviation in either direction (89). We will proceed with modeling prediction error effects if more than 10% of exposures meet the above prediction error criteria (49).

The primary aim of the study is to explore how prediction error during exposures relates to session-by-session symptom change. Exposures may occur from sessions 5 to 12. The outcomes are measured once at each session, but the number of exposures completed may vary significantly over treatment. We will aggregate EMA data obtained between sessions (e.g., between sessions 5 and 6, or 6 and 7, etc.) to form seven time points. Symptoms at time *t* will be regressed onto the mean P and mean O in the preceding inter-session interval (i.e., between *t* – 1 and *t*). We will control for the effect of symptoms at the preceding session (*t* – 1) and other theoretically relevant exposure mechanisms, specifically mean fear activation (operationalized as mean peak anxiety minus mean pre anxiety) and mean within-exposure habituation (operationalized as mean peak anxiety minus mean end anxiety) in the preceding inter-session interval. Operationalizing fear activation and habituation in these ways is consistent with most prior research, but we acknowledge the limitations of these indices noted by Bonito et al. (38) and will discuss the results in light of these.

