In line with learning theory, we hypothesize that people whose exposures since the last session (*t* – 1) went better than expected will have lower social anxiety symptoms and social threat appraisals at the next session (*t*). Specifically, when holding mean O and other controls constant, higher mean P in the preceding inter-session interval (i.e., between *t* – 1 and *t*) will be associated with lower social anxiety symptoms and social threat appraisals at the next assessment (*t*), on average. Conversely, when holding mean O and other controls constant, lower mean P will be associated with higher social anxiety symptoms and higher social threat appraisals at the next assessment, on average.

Hypotheses will be supported if both the following conditions are met; (1) the fixed effect coefficient for mean O is significantly different from zero and positive in sign and (2) the fixed effect coefficient for mean P is significantly different from zero and negative in sign (52). To determine whether the joint effect of these component variables on the outcome variable is more complex than a linear discrepancy effect, we will run a model including second-order terms (mean P^2^, mean P × mean O, mean O^2^) as predictors (47, 50, 53). Hypotheses will be supported if the simpler model fits the data better than the more complex model. Models will be run in R using the nlme or lmer package. We will use the maximum likelihood estimation method and compare model fit using likelihood-ratio tests.

We will separate within- and between-person information for all time-varying predictors using person-mean centering (90). In this method, the person-mean centered predictors are added to level one and their respective person-means are added to level two. The fixed effect coefficients for the person-mean centered predictors are estimates of purely within-person effects, without being confounded with between-person effects.

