We will also consider whether time trends are present in the data by regressing social anxiety and exposure process variables on time in separate analyses. The presence of time trends in time-varying outcomes or predictors can potentially confound any observed relationships between these variables (56). In this study, treatment is designed to cause changes to the outcomes and predictors over time and these changes are of direct theoretical interest. In these circumstances, time de-trending is not recommended because it may artificially suppress the predictor coefficients of interest (90). To be conservative, if there are time trends in any of the predictors or outcomes, we will run a sensitivity test on the final models to determine whether the effects of interest remain after time detrending (by adding time as a covariate) (55, 90).

In principle, the data structure has a three-level nested structure where assessments are nested in participants who are nested in therapists. There may be some degree of correlation between participant assessments within-therapist (91). Therapist-related statistical dependency and therapist effects can be addressed using three-level models (assessments at level one, participants at level two, and therapists at level three). If each therapist in the study has at least two participants, then three-level models will be used (assessments at level one, participants at level two, and therapists at level three). Otherwise, two-level models will be used (assessments at level one and participants at level two) since it would not be possible to distinguish between therapist and participant variance (91). Some therapists may be more effective than others and it is possible (but not plausible) that therapists could moderate the effect of prediction error on the outcome. However, exploring therapist effects is beyond the scope of this study.

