The secondary aim of the study is whether the average prediction error experienced during treatment predicts treatment outcome. We hypothesize that participants who experienced greater symptom improvements from baseline to 3-month follow-up will have experienced greater overall threat prediction error in their exposures during treatment. For each participant, we will calculate their mean P and O experienced across all exposures in treatment (termed txP and txO, respectively). The outcome will be symptoms at 16 time points from baseline to 3-month follow-up. We will examine the interaction of assessment point with txP and the interaction of assessment point with txO on the outcome. The hypothesis would be supported if both interactions were significant, and txO is positive in sign and txP is negative in sign. The secondary hypotheses will be exploratory because cross-level interactions likely require larger sample sizes to be adequately powered to detect a medium effect size (92).

The tertiary aim of the study is to explore whether prediction error relates to surprise and learning outcomes. We hypothesize that the larger prediction error (regardless of type) will predict larger feelings of surprise after an exposure and greater likelihood for participants to report a learning outcome. We will use the EMA data without aggregation to perform multi-level RSA with surprise as the outcome and P and O and their higher order terms as predictors. Response surface parameters will be examined to determine whether the hypothesis is supported (49, 50, 53).

We will test whether session modality (in-person vs. video teleconference) affects outcomes by adding it as a level one predictor to all final models. We retain it as a control variable if it improves model fit. We will check the internal consistency of the threat prediction and outcome measures (other exposure measures are single item) using multilevel modeling [see (93)]. We will check the validity of exposure process measures by looking for expected patterns of associations among these variables (94).

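### The tertiary exposure-level analysis has no session or interval level in its stated nesting, so standard errors can be too narrow, mainly for session modality and little for the mismatch curvature

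*Protocol article*

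**What the plan says.** All references are to the protocol article.

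- **Nesting (Analysis).** The article says that in principle "the data structure has a three-level nested structure where assessments are nested in participants who are nested in therapists". If not every therapist has at least two participants, "two-level models will be used (assessments at level one and participants at level two".
- **Centering (Analysis).** "We will separate within- and between-person information for all time-varying predictors using person-mean centering". No centering on the session or interval mean is described.
- **Primary analysis.** Exposure surveys are averaged between sessions "to form seven time points", so there is one row per participant and interval.
- **Tertiary analysis.** "The tertiary aim of the study is to explore whether prediction error relates to surprise and learning outcomes". The unit then changes: "We will use the EMA data without aggregation to perform multi-level RSA with surprise as the outcome". No further level is named.
- **Modality (Analysis).** In-person or video delivery is entered at level one in all final models and kept if it improves fit.
- **Where exposures cluster (Exposure interventions).** Session 9 has "two exposures to complete with the therapist and two to complete individually during the session", four in all. In session 6, "Participants complete a social activity twice, once using safety behaviors and once without". Homework exposures run from session 5 onward, in numbers expected to differ between participants. The section on the momentary assessment procedure calls for a separate survey for each exposure within a session.

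**The concern.** The stated levels fit the primary analysis, where an assessment is an interval average. In the tertiary analysis an assessment is a single exposure, and exposures are grouped in sessions or intervals that lie between the exposure and the participant. Exposures in the same group share the stage of treatment and the participant's state at that time, and in-session ones also share the therapist contact and the mode of delivery. If P, O and surprise therefore move together within a group, a model without that level credits the data with more information than they hold.

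At stake are the tests of the response surface. The curvature along the mismatch line bears on whether larger prediction error goes with more surprise. The slope along that line bears on whether this holds for both types of error. The retain-or-drop decision on modality is also at stake, because modality does not vary within a session.

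**Working it through.** **The plan's own figure.** The tertiary analysis has none. The only power figure (Sample size) belongs to the primary analysis: 65 participants, 7 observations, effect 0.18, power 0.80. With SE = sqrt(slope variance/65 + 1/(65 × 6)), power = Φ(0.18/SE − 1.96). With zero slope variance SE = 0.0506 and power = 0.945. With slope variance 0.10, SE = 0.0641 and power = 0.80. The article does not give the slope variance, so 0.80 is neither confirmed nor refuted. Nothing below depends on it.

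**Inputs.** From the article: 65 participants and four exposures in session 9. Assumed, because the article gives no value: exposures per session or interval (m), and the share of within-person variance common to one interval, for the predictor (ρx) and for the surprise residual (ρe).

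**Formula.** With the interval level omitted,

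model SE / true SE = 1/sqrt(1 + (m − 1) × ρx × ρe).

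| m | ρx | ρe | Calculation | Ratio |
|---|---|---|---|---|
| any | 0 | any | 1/sqrt(1) | 1.00 |
| 2 | 0.2 | 0.1 | 1/sqrt(1.02) | 0.99 |
| 2 | 0.5 | 0.3 | 1/sqrt(1.15) | 0.93 |
| 4 | 0.2 | 0.3 | 1/sqrt(1.18) | 0.92 |
| 4 | 0.5 | 0.3 | 1/sqrt(1.45) | 0.83 |

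The product ρx × ρe is what matters. If P and O do not cluster by interval, their standard errors are right even when surprise does. In the last row the effective critical value is 1.96 × 0.83 = 1.63, a two-sided error of about 10%.

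Modality is constant within a session, so ρx = 1 for it. With m = 4 and ρe = 0.3 the ratio is 1/sqrt(1.90) = 0.73, an error of about 15%. Only surprise has to cluster.

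**Simulation with equal clusters.** 65 participants, 7 intervals, m = 2 or 4, ρx = 0, 0.2 or 0.5, ρe = 0.1 or 0.3, no true effects, person-mean centering, full second-order surface plus a session-level binary covariate, 1,500 runs per setting. The Monte Carlo standard error at 5% is sqrt(0.05 × 0.95/1500) = 0.6 points.

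- Linear P and O: about 5% when ρx = 0, and 10-11% in the worst setting.
- Mismatch curvature (P² − PO + O² coefficients): 4.6% to 6.9%, SE ratio 0.94 to 1.03.
- Session-level covariate: 5% to 17%, SE ratio 0.98 down to 0.69.
- With standard errors clustered on the participant: about 4% to 6.5% for every term.

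**Simulation with unequal clusters.** 65 participants and 8 session/interval bins. In-session exposures number 1, 1, 1, 1 and 4 in the first five bins, with about 2 homework exposures added in every bin. The interval share is the same for P, O and surprise. Rejection at nominal 5%:

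| Share | Linear P, O and mismatch slope | Mismatch curvature |
|---|---|---|
| 0.1 | about 5% | about 5-6% |
| 0.2 | 6-7% | about 5-6% |
| 0.3 | 8-9% | about 5-6% |
| 0.5 | 13-15% | about 8% |

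For modality the rates were about 12.5%, 15% and 21% at shares 0.2, 0.3 and 0.5. With a residual share of 0.3 and no clustering of P and O, the rate was still about 16%.

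**Adding the level.** In a smaller run (500 per setting, shares 0.3 to 0.5), a random intercept for interval brought rejection for the surface terms from 7-12% back to 3-7%.

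**The case against.** The strongest reply is that the random part of the tertiary model is never written out. The levels are described for assessments in general, before the tertiary aim is taken up, and an article may leave such detail to a fuller plan. This stands in part. But the article does more than stay silent: it states a nesting rule, then changes the unit of analysis to one the rule does not cover.

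Second, a reader might infer that exposures are treated as independent and that the error bars are therefore too narrow. The documents do not support that as fact. The participant level and the centering already absorb stable person differences. What is ignored is only extra same-interval correlation, and the article gives no value for it. At small shares the effect is negligible. This objection stands in full.

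Third, the clustering may be weak. Homework exposures in one interval need not share a day or a task, the session 9 exposures are deliberately varied, and whether session 6 yields one record or two depends on supplementary material not shown. This is fair, and shares near 0.5 in all three variables may well be high. Session 9 and the homework intervals still produce several records per group.

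Fourth, a falsely significant mismatch slope would count against the claim that the type of error does not matter, so over-rejection there does not manufacture support for the hypothesis. This is also correct.

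**Conclusion.** The point holds in a limited form. The stated levels do not cover exposures nested in sessions or intervals, so standard errors in the exposure-level models can be understated. For P, O and the mismatch slope this needs clustering in both predictors and surprise; the error rate runs from about 5% to 13-15% across assumed equal shares of 0.1 to 0.5. The curvature, which carries the main tertiary hypothesis, is little affected. Modality is the most exposed term, because clustering of surprise alone is enough to inflate its test. All cluster sizes and interval shares are assumptions.

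It would go too far to conclude that the surprise result is unreliable or that the study's main findings are at risk. The primary analysis has one row per interval and is untouched, and the tertiary aim is exploratory with no power claim. Severity is minor.

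**What to change.** In the exposure-level models, add a random intercept for session or inter-session interval within participant: exposures at level one, session or interval at level two, participants at level three, and therapists above them if that level is used. Person-clustered robust standard errors are an acceptable alternative. Either way, report the estimated share of within-person variance at the interval level, so that readers can see whether it mattered. Apply the same structure when modality is tested in these models.

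The cost is one term in the model statement. Surveys are time-stamped and record whether the exposure took place in or between sessions, so no new data are needed. If the interval variance is estimated as zero, the term can be dropped without loss.

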### Sample size

We used Arend and Shäfers’ (92) simulation-derived and case-sensitive guides to determine the sample size for adequate power in the primary analyses. We aim to recruit 65 participants so that for 7 observations per participant (data from sessions 5 to 12) in the primary analysis we could detect small-medium level one effects (standardized fixed-effect size = 0.18) with 0.8 power at a significance level of 0.05 and assuming a large intraclass coefficient of 0.5 (92). We plan to use full maximum likelihood estimation so that nested models that differ in fixed effects may be compared with likelihood ratio tests. The target sample size would be sufficient to provide accurate fixed effect estimates when using full maximum likelihood estimation, based on simulation-derived guidelines (95, 96).

If the actual sample size is low (less than 50), we will use restricted maximum likelihood estimation with small sample corrections so that estimation is unbiased (sample size as low as 15 can return accurate estimates with this method (96). In this case, for the primary analysis, we would focus on the core linear discrepancy model and conduct CRA. We would not be able to test whether complex or non-linear discrepancy models fit the data better than linear discrepancy effects because restricted maximum likelihood estimation doesn’t permit meaningful comparison of models that differ in fixed effects. Arend and Shäfers’(92) guidelines suggest that a medium level one effect could be detected with sample size as low as 30 people with 5 observations, 0.8 power at a 0.05 significance level, and large intraclass correlation (0.5).

Digital EMA is well accepted and feasible in psychiatric populations (97). However, missing data is expected and will be handled through maximum likelihood estimation, assuming it is missing at random (98).

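### Exploratory secondary analysis: a modality main effect, kept only if it improves fit, cannot adjust the two slope interactions for a different rate of improvement under video

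*Protocol article*

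**What the plan says.** All of the following stand in the Analysis section of the protocol article, unless another section is named.

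- Modality: "We will test whether session modality (in-person vs. video teleconference) affects outcomes by adding it as a level one predictor to all final models". The retention rule follows: "We retain it as a control variable if it improves model fit". No product of modality with assessment point is named anywhere.
- Secondary test: "We will examine the interaction of assessment point with txP and the interaction of assessment point with txO on the outcome". On the data used: "The outcome will be symptoms at 16 time points from baseline to 3-month follow-up". On the decision rule: "The hypothesis would be supported if both interactions were significant, and txO is positive in sign and txP is negative in sign".
- Status: "The secondary hypotheses will be exploratory because cross-level interactions likely require larger sample sizes to be adequately powered".
- How modality arises: under Treatment, it follows participant preference or COVID-19 rules, so it is not randomised. Under the changes due to the pandemic, in-person treatment was suspended from 20/3/2020 and approval to continue by video came on 8/4/2020.
- How modality could reach txP and txO: under Exposure interventions, the in-session exposures of sessions 5 to 8 "can be conducted over video teleconference through role plays with the therapist" or with confederates invited to the call. Homework exposures must respect any lockdown rules in force.

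**The concern.** The secondary question is whether symptoms fall faster in participants with higher average threat prediction and lower average threat outcome. That is a statement about slopes. A modality main effect allows video participants to sit higher or lower throughout, but holds their rate of improvement equal to that of in-person participants with the same txP and txO. Any real difference in rate has no term of its own, and the part that correlates with txP and txO loads onto the two tested interactions.

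The retention rule adds to this. It asks whether a level shift improves fit, so modality can be dropped in just the situation where it confounds the slopes. If it is kept, the interactions are still unadjusted. At stake is whether a difference between delivery modes could be read as a prediction-error effect in the secondary analysis.

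**Working it through.** **What there is to reproduce.** The plan gives no figure for the secondary slope test or for modality adjustment. Its power statement (Sample size: "We aim to recruit 65 participants so that for 7 observations per participant (data from sessions 5 to 12) in the primary analysis") concerns the primary analysis and does not bear on this point. The effect sizes below are therefore assumptions; N = 65 is the plan's target.

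**Step 1: size of the bias.** Let M = 1 for video (half the sample, variance 0.25). Let d be the slower improvement under video, in within-modality SDs of person slopes. Let a = (aP, aO) be the shifts that video causes in txP and txO, in SDs. Let W be the within-modality covariance of txP and txO, with unit variances and correlation 0.6. The true effect of txP and txO on slope is set to zero. With modality left out of the slope equation, the two slope coefficients become

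bias = d × 0.25 × W⁻¹a / (1 + 0.25 × a′W⁻¹a), with 1 − 0.6² = 0.64.

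- *Scenario A*, a = (−0.5, +0.3), d = 0.5. W⁻¹a = ((−0.5 − 0.18)/0.64, (0.3 + 0.30)/0.64) = (−1.0625, +0.9375). a′W⁻¹a = 0.8125 and the denominator is 1.203. Bias: 0.125 × (−1.0625)/1.203 = −0.11 for txP and 0.125 × 0.9375/1.203 = +0.10 for txO.
- *Scenario B*, a = (−0.8, +0.3), d = 0.8. W⁻¹a = (−1.531, +1.219), a′W⁻¹a = 1.591, denominator 1.398. Bias: 0.2 × (−1.531)/1.398 = −0.22 and 0.2 × 1.219/1.398 = +0.17.
- *Scenario C*, a = (−0.5, −0.5), d = 0.5. W⁻¹a = (−0.3125, −0.3125), a′W⁻¹a = 0.3125, denominator 1.078. Bias: −0.036 for both, so the txO term moves against the hypothesis.

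**Step 2: error rate under the plan's own rule.** Person slopes were simulated for 65 participants under the same assumptions and regressed on txP and txO. Support was declared only if both terms were significant (two-sided 0.05; sidedness is not stated in the plan) with the hypothesised signs.

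| Scenario | Joint false support, modality not in the slope equation |
|---|---|
| No confounding | about 0.6% |
| A: −0.5 / +0.3 / 0.5 slower | about 3.6% |
| B: −0.8 / +0.3 / 0.8 slower | about 12% |
| C: −0.5 / −0.5 / 0.5 slower | about 0.6% |

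Adding modality as a slope predictor returns the bias to about zero in all three.

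**Step 3: does the main effect help?** A separate simulation used the full layout: 65 participants, 16 equally spaced points, random intercept and slope, ICC 0.5, random-slope SD 0.5, txP–txO correlation 0.5. Here SDs are those of the outcome, and slowing is measured at the last point. With modality constant within a person, both interaction coefficients and their tests were identical with and without the main effect in every scenario. With video slower by 0.5 SD and opposite shifts of 0.8 SD in txP and txO, joint false support was 10.3% either way, and 0.5% once modality × assessment point was added.

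**Step 4: does the fit rule help?** In the runs where modality changed slope but not level, the main effect was significant in only 7–15%, so it would usually be dropped. With an added level effect of 0.4 SD it was significant in 61% of runs, yet joint false support was still 9.75%.

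**Step 5: modality that changes within a course.** With video slower by 0.8 SD, opposite 0.8 SD shifts and participants switching mode between sessions, the main effect left joint false support at 20.7%. A session-level modality × time product reduced it only to 5.8%. I re-ran this case with each person's share of video sessions and its product with time; the joint rate went back to the no-confounding level.

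**The case against.** The strongest reply is about size and standing.

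- *The decision rule protects.* Both interactions must be significant with opposite signs. A reader who looks at one term at a time might infer an error rate of about 10% in scenario A, or 32% (txP) and 20% (txO) in scenario B. Those are not rates of a wrong conclusion under this plan; the joint rates of about 3.6% and 12% are. In a 16-point mixed model with an assumed slope SD of 0.5, scenario A gives only about 1.6%. This stands.
- *The sign pattern is an assumption.* Material false support needs video to lower txP, raise txO and slow improvement, or the reverse of all three. The documents give no direction for any of these. A shift of both in the same direction is at least as plausible and produces almost no false support. This stands.
- *The route is partial.* Video role plays concern the in-session exposures of sessions 5 to 8, while txP and txO also average homework and session 9, which is carried out in real settings even when supported remotely. Treatment content was written to keep the modes consistent. This makes large shifts less likely. The lockdown limits on homework still give a second route, though one tied to calendar period.
- *The analysis is exploratory and the study is declared correlational.* True, and it lowers the severity. The exploratory label is justified by power, however, and the plan still fixes a support rule.

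None of this makes a level term adjust a slope. Nor is this a detail left open for a fuller plan: the article itself fixes the form of the modality term and its retention rule.

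**Conclusion.** The point holds as a minor one. In the secondary model the planned modality step cannot adjust assessment point × txP or assessment point × txO for a different rate of improvement under video, and its retention rule tests the wrong quantity. Bias follows only if modality is related both to rate of improvement and to txP or txO. That is plausible from how modality was assigned and how exposures were adapted, but no figure in the documents bears on it. The joint rates rest wholly on the assumed shifts, the half-and-half split and the correlation of 0.6.

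Two stronger readings should be resisted. A reader might infer that the primary analysis is exposed in the same way. It is not: that model conditions on symptoms at the preceding session, so a modality main effect there adjusts change between sessions. A reader might also infer that a supportive secondary result would be an artefact of delivery mode. The documents do not show that such confounding exists, only that the planned step could neither detect nor remove it.

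**What to change.** For the secondary model only, replace the modality step with a sentence such as: *each participant's share of sessions held by video, and its product with assessment point, are included in the model and kept whatever their effect on fit.*

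A person-level share suits this model for two reasons. It copes with participants who switch mode, where a session-level product removes only part of the bias. It is also defined at all 16 assessments, whereas 16 − 12 = 4 of them (baseline, mid-treatment, post-treatment, 3 months) are not sessions and have no natural session modality. Keep the main-effect form in the primary model.

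The cost is one sentence, two extra person-level coefficients and a slight loss of precision. The modality data are already needed for the step as planned.
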